### Intra- and post-operative care of the patients

Eligible patients who have given consent to participate in the study will receive routine pre- and intra-operative care. Anaesthesia will be induced intravenously using propofol and maintained using either sevoflurane or desflurane. Patients will receive an epidural catheter for intra- and post-operative analgesia unless contraindicated. Fentanyl will be used as an analgesic during induction, and rocuronium will be used as a muscle relaxant. Crystalloids and colloids will be used as resuscitation fluids intra-operatively at the discretion of the attending anaesthetist. A haemoglobin level of 80–90 g/L will be the transfusion trigger. Post-operative maintenance fluids will be a 2.5% or 5% glucose solution at a rate of 1 ml/kg/h. Analgesics may be given during the intervention phase of the study, and the rate of vasoactive agents may be adjusted to maintain mean arterial pressure >65 mmHg. No fluid other than maintenance and study fluids may be given during the intervention period.

### Randomisation and blinding

Patients are screened for indications for fluid administration during the first 5 h after admission to the PACU as described above. Patients who fulfil inclusion criteria and meet no exclusion criteria will be randomised using a sealed envelope to either rapid or slow infusion of study drug. The randomisation and preparation of sealed envelopes are performed by an independent party (Clinical Research Unit, Skåne University Hospital, Lund). Randomisation was performed using a computerised random number generator. The research team is blinded to block size. Measurements of plasma volumes, transcapillary escape rate (TER) for albumin and post-operative follow-up will be performed by members of the research team who are blinded to the treatment allocation.

### Study interventions

Patients randomised to a fast or slow infusion will receive 5% albumin at a dose of 10 ml/kg in 30 minutes or 180 minutes, respectively. Dose is based on ideal body weight [17]. At 240 minutes after the start of albumin infusion, the study protocol is completed, and the patient thereafter receives post-operative care according to local routine. Figure 2 shows a brief overview of the experimental protocol. Patients will be in lying position throughout study protocol time (240 minutes).

**Fig. 2 Fig2:**
[figure not shown]
Detailed experimental protocol. *PV1* Baseline plasma volume, *PV2* Plasma volume after 30 minutes, *PV3* Plasma volume after 180 minutes, *Hct* Haematocrit, *ScvO*
_*2*_ Central venous oxygen saturation, *BP* Blood pressure, *CVP* Central venous pressure, *HD* Hourly diuresis, *TER* Transcapillary escape rate

### Primary outcome

The primary outcome in the study is change in plasma volume 180 minutes after the start of the albumin infusion.

### Secondary outcomes

Secondary outcomes are differences in plasma volume over time (integral of plasma volume over time from the start of albumin infusion from plasma volume PV1 to PV3) and incidence of post-operative complications up to 30 days post-operatively (see Additional file 3 for definitions of complications). Other outcomes of interest are TER for albumin from 180–240 minutes after the start of albumin infusion, change in heart rate, change in central venous oxygen saturation, change in haemoglobin concentration in blood, change in blood pressure, change in central venous pressure, change in plasma lactate from the start of albumin infusion to 3 h after start of infusion, and diuresis from the start of albumin infusion to 3 h after the start of infusion.

In addition, exploratory analyses are planned. These analyses include measurement of effects of the different infusion rates on plasma concentration of markers of endothelial damage and on hormones involved in fluid homeostasis. For this purpose, blood samples are collected 5 minutes before centrifugation, and plasma samples will be stored following centrifugation at −80 °C until analysis. We also intend to analyse to what extent included patients are hypovolaemic at inclusion (>10% lower than calculated normal blood volume [18]).

### Data collection and management

All study data will be recorded in CRFs for each patient, which are kept at the study site. Information on co-morbidities, medications, results of pre-operative physical examinations, routine laboratory analysis results, American Society of Anesthesiologists physical status classifications, Physiological and Operative Severity Score for the enUmeration of Mortality and morbidity and Revised Cardiac Risk Index will be collected from the hospital electronic chart system. Peri-operative data will be collected from the anaesthesia chart, and data that will be registered include anaesthesia methods and drugs, type and volume of fluids, peri-operative bleeding, and diuresis. Inclusion criteria will be registered in CRFs before randomisation. Clinical haemodynamic evaluation will be performed and recorded at inclusion and at 180 minutes after the start of albumin infusion. Members of the research team have unlimited access to study data. The data collected in the present study will be available from the corresponding author on reasonable request. The auditing (see below) will include source data verification.

### Sample size

Published SD values for plasma volume measured with the ^125^I-HSA method are in the range of 4–7 ml/kg [22]. In the present study, we wish to compare differences in changes in plasma volume, and it is reasonable to assume that the SD is in the lower part of this range. In an experimental study, a 50% greater plasma volume expansion was found after slow administration of 5% albumin compared with a bolus dose of the same volume [10]. If we wish to detect a 40% difference in volume-expanding effect following administration of 10 ml/kg of 5% albumin, assuming that the SD of the plasma volume is 5, then about 30 patients in each group are required to obtain a power of 80%. To adjust for a slightly lower than expected treatment effect and for the possibility that patients may not complete the protocol, we intend to include a total of 70 patients: 35 patients in each arm. Should the number of patients who complete the protocol be <30 in any of the treatment groups, we plan to increase the sample size to maintain power.

### Statistical analysis plan

The study will continue until the planned number of patients has been included, unless the interim analysis indicates that the study should be stopped. Results will be unblinded when all data have been collected. Only patients who received 90% or more of the intended dose will be included in the analysis. The investigating team will perform the statistical analyses.

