**Methods/design:**

The study is a single-centre, assessor-blinded, parallel-group, randomised prospective study. Patients over 40 years of age admitted to the post-operative care unit after a Whipple procedure or major gynaecological surgery and presenting with signs of hypovolaemia are eligible for inclusion. Patients are randomised in a 1:1 fashion with no stratification to either rapid (30 minutes) or slow (180 minutes) infusion of 5% albumin at a dose of 10 ml/kg ideal body weight. Plasma volume is measured using ^125^I human serum albumin at baseline (prior to albumin infusion) as well as at 30 minutes and 180 minutes after infusion start. The primary endpoint is change in plasma volume from baseline to 180 minutes after the start of 5% albumin infusion. Secondary endpoints include the integral of plasma volume over time from baseline to 180 minutes after the start of the infusion and transcapillary escape rate of albumin (%/h) from 180 minutes to 240 minutes after the start of albumin infusion. In addition, diuresis, change in central venous oxygen saturation, lactate and blood pressure will be evaluated. A total of 70 patients will be included in the study, and the study has 80% power to detect a difference of 4 ml/kg in plasma volume expansion between the two groups.

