Fluid administration is one of the most common therapeutic interventions in ICUs and in post-operative units around the world [12], and a fluid bolus is a recommended method to assess fluid responsiveness. However, to date, no study has addressed the importance of infusion rates in a clinical setting. Although rapid correction of hypovolaemia makes intuitive sense, the need for further knowledge in this aspect of fluid resuscitation was highlighted by the recent Fluid Expansion as Supportive Therapy trial, which showed a surprising increase in mortality following a rapid administration of resuscitation fluids compared with less aggressive fluid resuscitation [13]. Based on these considerations, the primary objective of the present study is to test the hypothesis that plasma volume expansion of a given volume of colloid is greater if fluid is administered slowly rather than rapidly.

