### Informed consent and withdrawal

Patients scheduled for the operative procedures described above will be assessed for inclusion. If none of the pre-operative exclusion criteria are met, a member of the research team will provide both oral and written information before surgery (Additional file 2). All patients will be given the opportunity to ask questions about the study and will also be given sufficient time to decide whether to participate. Patients are informed of their right to withdraw from the study at any time. A patient who withdraws consent receives standard care. In addition, the patient/participant may be permanently withdrawn at the investigator’s or the treating physician’s discretion at any time if this is considered to be in the patient’s best interest. Predefined permanent withdrawal criteria are as follows:Change of surgery procedure to other than operation ad modum Whipple or major gynaecological cancer surgerySerious violation of the study protocol, such as administration of other resuscitation fluid in a volume >200 ml within 3 h after start of albumin infusionOccurrence of known side effects, defined as serious adverse events (SAEs) listed in the summary of product characteristics of 5% albumin or SERALB-125® (IBA-CIS Bio International, Gif-Sur-Yvette, France) (Side effects that warrant permanent withdrawal include anaphylactic shock or pulmonary oedema.)

A record is kept of patients who consented in the pre-operative screening but were never enrolled (patient screening log).

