#### General analytical principles

Analysis will be performed on a per-protocol basis.All hypothesis tests will be two-sided, with a maximal type I error risk of 0.05.Subgroup analysis will be performed regardless of overall treatment efficacy.Imputation will not be used to correct for missing data in the analysis.

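### The only stated analysis is per-protocol, with patients removed by post-randomisation events that may differ between infusion rates, so both the plasma-volume and the complications comparison are open to selection bias

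*Protocol article*

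**What the plan says.** *Statistical analysis plan*: "Only patients who received 90% or more of the intended dose will be included in the analysis". *General analytical principles*: "Analysis will be performed on a per-protocol basis", and "Imputation will not be used to correct for missing data in the analysis".

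*Informed consent and withdrawal* lists the events that end participation. One is more than 200 ml of other resuscitation fluid within 3 h of the start of albumin. Another is a known serious side effect: "Side effects that warrant permanent withdrawal include anaphylactic shock or pulmonary oedema". A patient may also be "permanently withdrawn at the investigator’s or the treating physician’s discretion at any time". A change of surgical procedure is listed too, but it precedes randomisation and is not at issue.

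*Study interventions*: patients receive "5% albumin at a dose of 10 ml/kg in 30 minutes or 180 minutes, respectively". The abstract says: "The study is a single-centre, assessor-blinded, parallel-group, randomised prospective study". *Randomisation and blinding* describes blinding only for the staff who do the measurements and the follow-up.

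The baseline table (*Assessment of baseline variables*) is limited to patients who fulfilled the protocol. The one sensitivity analysis (*Subgroup analysis*) is a regression on type of surgery and baseline plasma volume, which leaves the analysis set unchanged. *Analysis of outcomes* exempts the number of complications from exploratory status, and nothing exempts complications from the analysis-set rule.

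**The concern.** Randomisation makes the two groups comparable as randomised. Once membership of the analysis set depends on what happens during the infusion, that protection holds only if the exclusions are unrelated to outcome or act alike in both arms. This design gives reasons to doubt it:

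- **Dose rule.** The slow arm can be interrupted for much longer before it reaches 90% of the dose.
- **Extra-fluid rule.** All patients enter with an indication for fluid, and for most of the 3 h window a slow-arm patient has received less of it.
- **Side effects.** Pulmonary oedema could plausibly depend on infusion rate.
- **Discretion.** A 30- or 180-minute infusion is visible at the bedside, and the treating physician may withdraw a patient.

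At stake are the type I error of the primary comparison, which the plan caps at 0.05, and the fairness of the 30-day complications comparison. As written, a patient withdrawn for pulmonary oedema would drop out of the very comparison meant to count complications.

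**Working it through.** **Inputs from the article.** SD 5 and difference 4 ml/kg (*Sample size*, *Interim analysis*), two-sided 0.05, Student's t test, 35 per arm with about 30 required.

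**The plan's own figure.** n = 2(1.960 + 0.842)² × 5² / 4² = 24.5, so 25 per arm, or 26 with the t distribution. The plan says about 30, which is on the safe side and does not affect this point. Power for 4 ml/kg is 86% with 30 per arm and 91% with 35.

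**Exposure to the rules** (constant infusion rate assumed).
- 90% of the dose is reached at 0.9 × 30 = 27 min in the rapid arm and 0.9 × 180 = 162 min in the slow arm.
- At 30 min the rapid arm has received 10 ml/kg and the slow arm 10 × 30/180 = 1.7 ml/kg.

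**Bias by formula.** Suppose k of 35 patients are excluded from one arm and their mean expansion is D ml/kg below that of the retained patients. With no true effect the spurious difference is b = (k/35) × D. Type I error follows from the noncentral t distribution with noncentrality b / [5√(1/(35−k) + 1/35)]. For k = 5 and D = 5, b = 0.71, the standard error is 5√(1/30 + 1/35) = 1.24 and the noncentrality is 0.57.

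| k | D (assumed) | b (ml/kg) | Type I error |
|---|---|---|---|
| 1 | 5 | 0.14 | 5.2% |
| 3 | 5 | 0.43 | 6.4% |
| 5 | 5 | 0.71 | 8.7% |
| 5 | 10 | 1.43 | 20.5% |

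**Bias by simulation.** No true effect. The excluded patients are those lowest on a latent trait that correlates 0.5, 0.7 or 1.0 with expansion.

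| Excluded, one arm / other arm | Spurious difference (ml/kg) | Type I error |
|---|---|---|
| 1 / 0 | up to 0.31 | about 5 to 6.5% |
| 3 / 0 | 0.40, 0.57, 0.82 | 6.4%, 8.2%, 12.0% |
| 5 / 0 | 0.64, 0.90, 1.28 | 8.5%, 12.2%, 20.8% |
| 5 / 3 | 0.24, 0.33, 0.46 | about 6 to 10% |

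The differences in the last row are the 5 / 0 row minus the 3 / 0 row.

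**The other direction.** If the true difference is 4 ml/kg and the lowest responders are lost from the inferior arm, power falls from 91% to 87%, 77% or 64% with 1, 3 or 5 exclusions.

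**Can the planned size carry an all-treated analysis?** If 5 of 35 patients contribute no effect, the mean difference is 4 × (1 − 5/35) = 3.43 ml/kg and power is 81%, provided plasma volume at 180 min (PV3) is measured in all of them.

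**What extra fluid does to PV3.** Assume 65 kg ideal weight. Then 200 to 500 ml is 3.1 to 7.7 ml/kg. If 5 of 35 patients receive it and 50 to 100% is retained, the arm mean shifts by (5/35) × 3.1 × 0.5 = 0.2 up to (5/35) × 7.7 × 1.0 = 1.1 ml/kg.

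**The case against.** The strongest reply is that the question is physiological: whether "plasma volume expansion of a given volume of colloid is greater if fluid is administered slowly rather than rapidly". A patient given half the dose, or a substantial volume of another fluid, says little about that. This stands as a reason to keep the per-protocol set. It does not justify making it the only analysis, because the patients left after exclusion are no longer the randomised groups.

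A second reply is that including patients who received extra fluid brings its own bias. This also stands. Such fluid raises PV3 directly, by an amount comparable to the selection bias computed above. A reader might suppose that a broader analysis set only dilutes the effect; that is true of incomplete dosing but not of extra fluid.

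Third, the article has safeguards. Patients whose physician strongly prefers another fluid, rate or volume are excluded beforehand. Other fluids are barred during the intervention, while vasoactive drugs may be adjusted. The CONSORT chart will give numbers randomised and completing by arm. *Trial status* reports no serious adverse events, so the side-effect route may have removed nobody. These make large losses less likely. They do not close the dose, fluid and discretion routes, and completer counts show neither the reasons nor the outcomes of those removed. The top-up to 30 completers protects power, not comparability.

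Fourth, a reader might infer that the bias favours slow infusion, because under-filled slow-arm patients would be the ones removed. The documents do not support this. No exclusion counts are given, dependence on arm is inferred from the design, and losses from overload in the rapid arm could act the other way.

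**Conclusion.** The point holds. Per-protocol is the only analysis stated for a superiority hypothesis, and membership of that set depends on events after randomisation, under staff not described as blinded. The article does not spell out how each withdrawal criterion maps to the analysis set. The dose rule is explicit, and the others enter through the per-protocol principle.

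The size is conditional on assumed counts and an assumed link with outcome. It is minor for a single exclusion and material for three to five concentrated in one arm. It is smaller when both arms lose patients.

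A reader might take the 21% figure as the expected error rate, on the ground that 35 against 30 is the plan's own allowance. That is not supported. The allowance covers both arms and also a treatment effect slightly smaller than expected. A correlation of 1.0 is a limiting case, since plasma volume comes from a gamma-counter assay by blinded staff. The direction remains undetermined.

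**What to change.** Before unblinding:

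- Make the primary analysis all randomised patients in whom albumin was started, in the assigned arm, using every available PV1 (baseline) and PV3.
- State that PV3 is still obtained after a protocol deviation where the patient consents. Recruitment is reported as complete, so this can act only on patients added under the top-up rule. For the others, report by arm how many have PV3.
- Analyse 30-day complications, and tabulate baseline variables, in all randomised patients.
- Keep the set with at least 90% of the dose as a pre-specified sensitivity analysis that addresses the fixed-volume question.
- Report exclusions, their reasons and the volume of extra fluid by arm.
- State that a conclusion will be drawn only if the two analyses agree.

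The cost is mainly wording. Incomplete dosing may dilute the effect, and extra fluid may shift an arm mean by roughly 0.2 to 1.1 ml/kg under the assumptions above, which is why neither analysis can stand alone. Requiring a measured PV3 is itself a selection after randomisation, so the broader set reduces the problem without removing it.

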#### General analytical principles

Analysis will be performed on a per-protocol basis.All hypothesis tests will be two-sided, with a maximal type I error risk of 0.05.Subgroup analysis will be performed regardless of overall treatment efficacy.Imputation will not be used to correct for missing data in the analysis.

#### Assessment of baseline variables

Baseline variables of patients fulfilling study protocol in the two study arms will be tabulated. Discrete variables will be reported as frequencies and percentages, and continuous variables will be reported as either means with SDs or medians with interquartile ranges.

#### Analysis of outcomes

The primary outcome will be analysed using Student’s *t* test. Secondary outcomes will be analysed using Student’s *t* test or the Mann-Whitney *U* test as appropriate. Differences between the groups will be reported as means with 95% confidence intervals. In the event of no difference between the groups with regard to primary outcome and a difference in the secondary outcome of plasma volume over time, we will interpret these results as supporting our hypothesis but that confirmatory studies are needed. With the exception of number of complications, all other outcomes are regarded as exploratory, and no emphasis will be placed on differences between the treatment groups, should the primary outcome and plasma volume over time outcome be negative.

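### The fallback rule for a null primary names no direction, and the 0–180 minute plasma volume integral it relies on favours the rapid arm by construction

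*Protocol article*

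**What the plan says.** The Background section states a one-directional hypothesis: "plasma volume expansion of a given volume of colloid is greater if fluid is administered slowly rather than rapidly". The primary outcome is "change in plasma volume 180 minutes after the start of the albumin infusion". One secondary outcome is the "integral of plasma volume over time from the start of albumin infusion from plasma volume PV1 to PV3", and the legend to Fig. 2 defines PV3 as "Plasma volume after 180 minutes". Under Study interventions, patients receive "5% albumin at a dose of 10 ml/kg in 30 minutes or 180 minutes, respectively" according to arm.

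Under Analysis of outcomes, the plan covers the case of no difference in the primary outcome. If there is then "a difference in the secondary outcome of plasma volume over time, we will interpret these results as supporting our hypothesis", though confirmatory studies would be needed. Under General analytical principles, "All hypothesis tests will be two-sided, with a maximal type I error risk of 0.05". Nowhere does the article say that the difference in the integral must favour slow infusion, and nowhere is the integral adjusted for fluid not yet infused.

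**The concern.** The rule ties a result without a direction to a hypothesis that has one. That would be a small wording gap if the integral could go either way. It is more than that here, because the two arms receive the same volume on very different timetables within the window being integrated. For most of the 180 minutes the rapid arm holds fluid that the slow arm has not yet been given. The integral therefore mostly measures when the fluid was given and says little about how well it was retained.

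The rule applies only when the primary is null, the very situation in which a contrary statement of support would do most harm. The same paragraph also lets the integral decide, together with the primary, whether the exploratory outcomes receive any emphasis.

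**Working it through.** **Inputs.** Dose 10 ml/kg in both arms, infused over 0.5 h or 3 h (Study interventions). Integration window 0–3 h (Secondary outcomes; Fig. 2 legend). Design effect 4 ml/kg (Abstract: "the study has 80% power to detect a difference of 4 ml/kg in plasma volume expansion between the two groups"), which is 40% of 10 ml/kg as in Sample size. Planned 35 per arm, and published SD of plasma volume 4–7 ml/kg (Sample size). The plan gives no figure for the integral, so there is none to reproduce.

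**Assumptions, not in the documents.** Gain above baseline never exceeds infused volume; infusion is at a constant rate; loss is first-order at rate k per hour.

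**Formulas.** With infusion time T and r = 10/T:
- Gain at end of infusion: P = (r/k)(1 − e^(−kT)).
- Area during infusion: (r/k)[T − (1 − e^(−kT))/k].
- Area afterwards: (P/k)(1 − e^(−k(3−T))).
- With k = 0, the total is 10T/2 + 10(3 − T).

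**No loss.** Rapid: 10×0.5/2 + 10×2.5 = 27.5. Slow: 10×3/2 = 15.0 ml·h/kg. The gap of 12.5 over 3 h is a time-averaged 4.17 ml/kg in favour of rapid, while the gains at 180 minutes are identical.

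| Scenario | Gain at 180 min, rapid / slow (ml/kg) | Area, rapid / slow (ml·h/kg) |
|---|---|---|
| No loss | 10 / 10 | 27.5 / 15.0 |
| 15%/h loss in both arms | 6.6 / 8.1 | 22.5 / 13.0 |
| 35%/h loss in both arms | 3.8 / 6.2 | 17.6 / 10.9 |
| Design effect (rapid k = 0.186, slow k = 0) | 6 / 10 | 21.5 / 15.0 |
| Equal gain of 8 at 180 min | 8 / 8 | 24.6 / 12.9 |

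In rows 2 to 4 slow infusion does better at 180 minutes, as hypothesised, and the integral still favours rapid.

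**What would reverse it.** Against a slow arm that loses nothing, the areas are equal only when the rapid arm loses 0.496 per hour. That leaves 2.6 of 10 ml/kg at 180 minutes, a deficit of 7.4 ml/kg, or 7.4/4 = 1.9 times the design effect.

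The direction does not depend on first-order loss. Join the points by straight lines, with rapid gain P at 30 minutes and E at 180. In ml·min/kg, the rapid area is 15P + 75(P + E) = 90P + 75E, and the slow area with gain E at 180 minutes is 90E. With equal gains at 180 minutes, rapid is larger unless P < E/6. At the design effect, equality needs 90P + 75×6 = 900, so P = 5, which is below the rapid arm's own later gain of 6.

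**Chance of a significant difference.** No SD for the integral is given. If 4–7 ml/kg is taken as the SD of time-averaged volume, the SD of the integral is 3×4 to 3×7, that is 12–21 ml·h/kg. Two-sided t test at 0.05, 35 per arm:
- No loss, difference 12.5: 0.99 to 0.69.
- 15%/h, difference 9.5: 0.91 to 0.47.
- 35%/h, difference 6.8: 0.64 to 0.26.

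In each case the expected difference favours rapid. Integrating absolute plasma volume adds 3 h × baseline to both arms, which leaves the expected difference unchanged but may increase the variance.

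**The case against.** The strongest reply is that the hypothesis is plainly one-directional, so a result that supports it can sensibly only mean a difference towards slow infusion. Two-sided testing is standard and does not make interpretation blind to sign. The plan reports mean differences with 95% confidence intervals, so the sign would be visible, and it adds that confirmatory studies would be needed. All of that is fair, and the authors would probably notice a contrary sign. A reader might infer from the literal wording that a result favouring rapid infusion would in practice be published as support for slow; the documents do not show that.

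The reply does not rescue the rule. Restricted to slow greater than rapid, it can almost never be met. The caveat about confirmatory studies limits the strength of the claim without correcting its direction.

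A reader might also infer that a significant contrary result is close to certain. The documents do not support that either. The highest probabilities need zero leakage, in patients whom the Discussion describes as having vascular leak, and they rest on an assumed SD. An exactly null primary also occurs in the common-loss model only at zero loss; with any common loss the slow arm is somewhat higher at 180 minutes.

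**Conclusion.** The rule is wrong as written. It lacks a direction, and the outcome it rests on favours the rapid arm because of the infusion timetable: by 12.5 ml·h/kg with no loss, 9.5 at 15%/h in both arms, and 6.5 (21.5 − 15.0) when the full design effect for slow infusion is present. Taken literally, the likeliest significant difference is contrary to the hypothesis and counted as support; taken charitably, the fallback is practically unreachable.

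The direction rests on gain not exceeding infused volume, and holds across the loss rates examined. The chance of significance depends on unstated quantities: about 0.7–0.99 with no loss, 0.5–0.9 at 15%/h and 0.3–0.6 at 35%/h, for an assumed SD of 12–21 ml·h/kg. The primary outcome and its analysis are not affected, so this is a point that should be fixed and not one that undermines the trial.

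**What to change.** Before unblinding, amend the paragraph under Analysis of outcomes:
- State that only a significantly larger integral in the slow arm would count as support, and that a larger integral in the rapid arm is reported as not supporting the hypothesis.
- Remove the raw integral from its role as fallback evidence, and report it descriptively as average volume over the infusion period.
- Bring the sentence on emphasis for exploratory outcomes into line, since it also refers to the integral.

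Do not replace it with the ratio of expansion area to infused-volume area. With identical loss rates that ratio favours slow infusion: at 15%/h, 22.52/27.5 = 0.82 (rapid) against 12.98/15.0 = 0.87 (slow); at 35%/h, 17.65/27.5 = 0.64 against 10.88/15.0 = 0.73. The slow arm's fluid has simply had less time to leave.

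The cost is one paragraph of wording and no new data. Recruitment is complete, but the plan unblinds only once all data are collected, so the change should be dated and made before then. The downside is that the fallback route to a supportive statement is lost.
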